**III. Study site**

The study will be conducted in South Africa in Soweto and in the informal settlement of Orange Farm, just outside of Soweto. Based on data from a recently completed population survey, it is estimated that children under 5 years of age account for 11.8% of the total population of 1,02 million people [13]. A national census conducted in 1996 should allow us to delineate the demographics of this community in even greater detail.

Although there is an emerging middle-class in the community, the majority of the population is still considered to be of lower socioeconomic status. Unemployment is estimated at 40% and there is a high incidence of teenage pregnancies. Risk factors that predispose to pneumonia include overcrowded living conditions, indoor and outdoor pollution, exposure to passive smoking, overcrowded crèche facilities and an increasing HIV infection rate.

There are 12 major clinics and 5 mobile clinics in Soweto and 4 clinics in Orange Farm providing free primary health care to all children; some of these clinics also provide routine immunization services. Patients who require admission are referred to Chris Hani Baragwanath Hospital, an academic hospital associated with the University of the Witwatersrand. The hospital has in excess of 2300 inpatient beds, 200 of which are used for general pediatric admissions. Approximately 24,000 babies are born in Soweto annually, two-thirds of which occur at Chris Hani Baragwanath Hospital and the remainder at one of six health centers equipped for obstetrics. A few children that require admission may attend the two other pediatric departments associated with the University, namely Coronation and Johannesburg hospitals, both of which are based in close proximity to Soweto and are easily accessible by public transport. Each of these hospitals has 50 general pediatric beds; all of the hospitals have X-ray and comprehensive laboratory facilities.

In South Africa immunization of all children is performed at Government health centers; the national immunization coverage in the first year of life is estimated at 74% [18]. In Soweto the immunization coverage is approximately 97% [[name] manuscript in preparation]. The recent Phase II study of pneumococcal conjugate vaccine at Zola Clinic had a 98% compliance rate over the first 3 doses of vaccine.

In the proposed study, vaccination with pneumococcal conjugate vaccine will be performed at all clinics providing routine immunization services in Soweto and Orange Farm [Appendix 3]. Vaccination will be performed by nurses trained in the administration of childhood immunization and who are specifically employed for this trial.

Surveillance for study patients admitted to Chris Hani Baragwanath Hospital will be done by study pediatricians and assistants in collaboration with the attending pediatricians at the hospitals.

**IV. Subject eligibility**

Infants who present to one of the health centers providing routine immunization services in Soweto and Orange Farm will be eligible for study participation based upon the following criteria. To be eligible for inclusion and continued participation in the study the child must fulfil all of the inclusion criteria and have none of the exclusion criteria

**A. Inclusion Criteria**

1. Infants who are 5-12 weeks of age.

2. Signed parental consent following a detailed explanation of participation in the study.

**B. Exclusion Criteria**

1. Any child who has already received his/her first DTP immunization.

2. A child with a progressive neurological disorder or a history of uncontrolled epilepsy/ infantile spasms.

3. A child unlikely to receive 3 doses of the vaccine in the study area.

**C. Conditions which might require delaying administration of vaccination**

A child with an intercurrent illness that requires referral/admission to hospital.

**D. Contraindications for subsequent doses of the study vaccine**

1. An immediate anaphylactic or any other serious reaction to a prior dose of study vaccine.

2. Child is withdrawn from the study at the request of the parent/guardian, or as a recommendation from the Safety Monitoring Committee.

3. Development of a progressive neurological or seizure disorder.

4. Contraindications specified in the manufacturers’ package insert for DTP/Hib vaccine [TETRAMUNE ®, Appendix 5]

**V. Trial design**

**A. Enrolment**

All children presenting to immunization clinics in Soweto or Orange Farm [Appendix 3] for routine immunization at approximately 6 weeks of age will be evaluated for study participation. Children will qualify for enrolment by meeting all inclusion criteria and none of the exclusion criteria, as determined by obtaining a medical history and performing a physical examination prior to immunization. The parent/guardian must also give consent for the child to participate in the study. Staff hired specifically for the study will do recruitment, immunization (study and routine vaccines), and follow-up.

The annual birth cohort in Soweto is approximately 24,000. It is anticipated that the entire birth cohort over a two-year period will be recruited.

**B**. **Randomization**

Randomization will occur immediately after consent for study participation has been obtained from a parent/guardian and study eligibility confirmed. Subjects will be randomized in equal numbers to receive either the pneumococcal conjugate vaccine or placebo; the unique subject identification numbers will be assigned in sequence. Due to some mobility within Soweto, children may not always receive their routine immunizations at the same clinic. To facilitate this movement, children will be randomized at the time of their first immunization to one of 10 vaccination codes, designated 0-9. The vaccination code and subject ID number will be recorded on the child’s Road to Health card, on the clinic medical records, and on the clinic immunization register. Immunization sites will be provided with vials for each of the 10 vaccination codes, thereby allowing children to receive their study immunizations at any of the study sites. Randomization schemes for each recruitment site will be generated prior to the start of the study by a statistician from WLVP who is otherwise uninvolved with the study.

**C. Blinding**

This study is double-blind. Pneumococcal conjugate vaccine and placebo will be supplied in lyophilized form in precoded vials by WLVP. TETRAMUNE® will be supplied by WLVP in commercial vials and hepatitis B (Hep B) and oral polio vaccines (OPV) will be supplied according to usual practice in South Africa. The identity of the ten vaccination codes (placebo versus vaccine) will be maintained in confidence from the investigators, study nurses and other study staff, from the clinical monitors, and from the child’s parents/guardians. The Road to Health cards, although usually brought to the hospital with the child, are not kept as part of the hospital bed letters; therefore, the study pediatricians will be blinded to the code of the vaccine received by hospitalized study participants. In the event that safety issues warrant the unblinding of an individual subject or the entire study, the identity of the vaccination codes will be kept by a member of the Safety Monitoring Committee ([name]) and by an individual at WLVP not involved with the vaccine trial.

**D**. **Treatment period**

Each study subject will receive three injections of either pneumococcal conjugate vaccine or placebo, administered concurrently with TETRAMUNE®, OPV, and Hep B. The injections will be administered at approximately 6, 10, and 14 weeks of age, with a minimum interval of 3 weeks between each dose and all three doses must be completed by 9 months of age. Children not returning within 1 week of the appointed time for the second or third vaccinations will either be telephoned or visited at home.

**E. Control group**

In an effort to offer a potential benefit to those children randomized to receive placebo, Hib conjugate vaccine, included in TETRAMUNE®, will be given to all children in the study. Hib conjugate vaccine is not currently provided by the Expanded Programme on Immunization in South Africa. In addition, all of the children in the study who are admitted to the hospital with suspected infectious disease will receive an extensive diagnostic work-up to determine the etiology of their disease. The placebo group will serve as a control for evaluating the protective efficacy and safety of the nonavalent pneumococcal conjugate vaccine.

**F. Follow-up**

**1. Vaccine Safety**

Following each vaccination, the child will be monitored at the clinic for approximately 15 minutes for any immediate local and/or systemic reactions. The parent/guardian will also be asked to observe for untoward effects which might occur within one week of vaccination. If the parent/guardian has concern, they will be asked to report these reactions to the study nurse as soon as possible. Any child with a clinical event of concern to the parents will be evaluated by the study nurse or other medical personnel. In the event that the child is hospitalized, the parent will be asked to contact the investigator immediately. Study pediatricians will also be conducting daily surveillance for hospitalization of study participants. Participation in the vaccine study will be noted on the child’s Road to Health card, which is presented at hospital visits.

All efforts will be made to obtain follow-up information on deaths which occur outside of the hospital through death notifications, cemetary records, etc..

The frequency of adverse events following vaccination will be assessed for both the placebo and treatment groups.

**2. Vaccine Immunogenicity**

To confirm the immunogenicity of the vaccine, a subset of 200 children will be randomly-selected from the pool of all children who have received 3 doses of the vaccine or placebo at any one of the study clinics. For logistical reasons, only those children receiving all 3 doses of the vaccine at the same clinic will be eligible for the immunogenicity study. At the 14 week visit, the parent/guardian will be asked to consent to have blood taken from their child at 18 weeks, 4 weeks after the third immunization. Serum antibody responses to the pneumococcal vaccine will be measured by standardized ELISA methods. Anonymous and confidential HIV testing will also be performed to obtain an estimate of the HIV seroprevalence of children in the study. The randomization scheme for selection of children to participate in the immunogenicity study will be developed by WLVP prior to initiation of the trial. The data from the immunogenicity study will be kept confidential from the study investigators until the end of the trial; however, the information will be provided to the Safety Monitoring Committee.

The immunogenicity study will be repeated when each additional lot of pneumococcal conjugate vaccine is introduced into the study.

**3. Vaccine Efficacy**

The statistical methods for calculating the efficacy of the nonavalent pneumococcal conjugate vaccine are described in Section XII. Vaccine efficacy will bedefined as the number of cases of culture-confirmed invasive pneumococcal disease or pneumonia in the HIV-negative group receiving the pneumococcal conjugate vaccine compared to the number of cases occurring in the placebo group. The study pediatricians will conduct daily surveillance for cases of severe pneumonia, as defined in Section VIII, at Chris Hani Baragwanath Hospital. In addition, a list of all cases of culture-confirmed pneumococcal disease will be obtained daily from the hospital microbiology laboratories. HIV testing will be performed in an anonymous manner for all children with study outcomes who are not tested for HIV during hospitalization. Those outcome cases with no HIV test results will be excluded from the efficacy analyses.

**G. Termination of follow-up for outcome surveillance**

Follow-up for any individual child will end when:

1. The study participant dies.

2. The Safety Monitoring Committee recommends early termination of the trial due to questions of vaccine safety or lack of efficacy.

3. The follow-up of study participants has been completed and the study is terminated.

4. If the child is lost to follow-up (moved out of the study area) and efforts to determine outcome status have been unsuccessful.

**VI. Conduct of the study**

**A. Enrolment**

1. Children approximately 6 weeks of age, operationally defined as 5-12 weeks of age, will be recruited at clinics performing routine immunizations in Soweto and Orange Farm. A list of the clinics is found in Appendix 3.

2. Prior to study enrolment, the child must undergo a physical examination and have a medical history obtained to ensure that he/she meets all inclusion criteria and none of the exclusion criteria.

3. The parent/guardian accompanying the child to the clinic will be informed of the study and, if they agree to have their child participate, will be asked to read and sign the informed consent. The informed consent will be reviewed and approved by the University of the Witwatersrand Committee for Research on Human Subjects and WLVP and will be available in English, Sesotho, Zulu, and Xhosa (see Appendix 6).

4. Children meeting the enrolment criteria will be randomized at each study site by assignment of the next sequential study identification number and corresponding vaccination code from a preprinted randomization list. Stickers indicating study participation, the study identification number, and the child’s vaccination code will be put on the child’s clinic medical records and on the Road to Health card. A separate Immunization Register containing the child’s and mothers name, address, child’s birthdate, study identification number, vaccination code, and dates of individual vaccine doses will be kept at each clinic.

**B.** **Administration of initial and subsequent vaccinations**

1. A medical assessment will be conducted before administration of each dose of test vaccine to ensure that the child continues to meet all of the inclusion criteria and none of the exclusion criteria.

2. The study nurse will determine which study vaccine to give from the Road to Health card. If the card is not brought to the clinic, the vaccination code will be determined from the clinic immunization register. In the event that the child presents to a different clinic and the Road to Health card is not available, the nurse will telephone either the clinic which initially randomized the child or will call the data management center who will determine the child’s vaccination code from the study computer database.

3. The preferred schedule is for subjects to receive their vaccines concurrently according to routinely scheduled vaccine timetables (see below), i.e., at 6, 10, and 14 weeks of age, with a minimum interval of 3 weeks between immunizations. The 2nd and/or 3rd doses of pneumococcal conjugate vaccine/placebo, however, can be given nonconcurrently from the other vaccines. All three doses of the conjugate vaccine/placebo must be completed by 9 months of age. The above constitutes “per protocol” vaccination schedule.

|  | **BCG** | **Tetramune** | **Hep B** | **OPV** | **Pneumo/**  **placebo** | **Measles** |
| --- | --- | --- | --- | --- | --- | --- |
| **Birth** | ***** |  |  | ***** |  |  |
| **6 weeks** |  | ***** | ***** | ***** | ***** |  |
| **10 weeks** |  | ***** | ***** | ***** | ***** |  |
| **14 weeks** |  | ***** | ***** | ***** | ***** |  |
| **9 mos** |  |  |  |  |  | ***** |
| **18 mos** |  | ***** |  | ***** |  |  |

The 0.5 ml of TETRAMUNE and 0.5 ml of Hep B vaccines will be administered intramuscularly using separate syringes with a 23 or 25-gauge needle in the anterio-lateral aspect of the right upper and right lower thigh respectively. The 0.5 ml of the trial vaccine will be administered in the anterio-lateral aspect of the left thigh. OPV will be orally administered. Standard immunization practices will be ensured. Epinephrine 1:1000 (1 mg/ml) and resuscitative equipment will be available in the event of an anaphylactic reaction. Vaccination Report Forms will be completed by the study nurse after each immunization.

4. The individual immunization clinics in Soweto are experienced in following children who have not returned for their scheduled routine vaccinations. Immunization registers will be used for follow-up of subsequent vaccinations. Each day the study nurse will review the register, record those patients who have been immunized on that day, and identify those patients who failed to attend. The study nurse will also be provided with a weekly list of all children enrolled at their site who were immunized the previous week at another study site. If telephone numbers are available, the study nurse will telephone parents of children who have failed to attend and remind them of the child’s clinic appointment. If no telephone number is available, the study nurse will make a home visit to the family. If a subject is withdrawn from the study, the circumstances will be documented in the Vaccination Report form.

5. In the rare cases of errors in vaccinating a child with vaccine of the wrong code (deviation from the randomization schedule), the subsequent doses should be the vaccine of the same code as the first dose. These children will not be included in the primary efficacy analysis. They will be included in the intent-to-treat analysis in the group based on the vaccine they receive as the first dose.

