**B. The secondary objectives of the study**  **are:**

**HIV-uninfected children**

1. To evaluate the efficacy of the pneumococcal conjugate vaccine on the incidence of invasive pneumococcal disease due to all pneumococcal serotypes in HIV-uninfected children who have received three doses of study vaccine per protocol.

2. To evaluate the efficacy of two or more doses of the pneumococcal conjugate vaccine against vaccine serotype-specific invasive disease and against hospitalized pneumonia.

3 To determine the protective efficacy of the pneumococcal conjugate vaccine against vaccine serotype-specific invasive disease in an ‘intent-to-treat’ analysis, i.e., analysis including all randomized children receiving at least one dose of study vaccine.

4. To further assess the safety and immunogenicity of the conjugate pneumococcal vaccine.

5. To derive a population-based serological correlate of protection.

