**C. Secondary efficacy outcome variables and statistical analyses**

The following efficacy outcome variables will also be evaluated for HIV-seronegative children. The analyses will include the graded ARI case definitions listed in VIII C.2. The primary outcomes (see above) and secondary outcomes 1 and 2 below will also be evaluated for children infected with HIV (see E below) as secondary analyses. The power for these analyses will depend on the number of outcome cases meeting the definition for inclusion in the particular analysis.

1. All invasive pneumococcal disease, including nonvaccine serotypes, in children who complete three doses of vaccine. This analysis will be performed using the methods and case definitions described above for the primary outcomes and include all first episodes of pneumococcal disease, regardless of serotype.

2. Vaccine-serotype invasive pneumococcal disease in children who complete at least two doses of vaccine, the first episode of disease occurring at least 14 days after the 2nd dose of vaccine. Exact binomial tests, including children who meet the case definitions described above and who have received either 2 or 3 doses of the vaccine, will be used as for the primary outcome analyses.

3. Vaccine-serotype invasive pneumococcal disease in all children who have received at least one dose of vaccine in the study regardless of immunization status (intent-to-treat analysis for vaccine-serotype pneumococcal disease). The intent-to-treat analysis will include the first episode of vaccine-serotype pneumococcal disease in children who were initially randomized into the study and received at least one dose of study vaccine and regardless of the number of vaccine doses they eventually received or whether they voluntarily withdrew from the study and were lost to follow-up. The null hypothesis of no difference between the two groups in all randomized chldren will be tested.

4. Vaccine immunogenicity will be assessed in a random sample of 400 children over the study period, or 200 children per lot of study vaccine introduced into the trial. The geometric mean titers of the antipneumococcal antibodies and 95% confidence interval of the vaccinated children will be determined and the distribution will be examined using reverse cumulative plots. The different response distributions of vaccine lots will be compared.

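### The intent-to-treat analysis counts a child whose first dose came from an opposite-arm code by the vaccine given, not by the arm randomised

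*Protocol*

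**What the plan says.** Protocol section VI.A item 4 has eligible children "randomized at each study site by assignment of the next sequential study identification number and corresponding vaccination code from a preprinted randomization list". Section V.B places this step directly after consent and confirmed eligibility, and spreads the two arms over ten vaccination codes.

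Section VI.B item 5 covers mistakes. It begins "In the rare cases of errors in vaccinating a child with vaccine of the wrong code (deviation from the randomization schedule" and sets three rules:

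- for later doses, "the subsequent doses should be the vaccine of the same code as the first dose";
- for the primary analysis, "These children will not be included in the primary efficacy analysis";
- for the secondary analysis, "They will be included in the intent-to-treat analysis in the group based on the vaccine they receive as the first dose".

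The intent-to-treat analysis is described in two further places. Section II.B, item 3 for HIV-uninfected children, calls it an "analysis including all randomized children receiving at least one dose of study vaccine". Section IX.C item 3 says "The intent-to-treat analysis will include the first episode of vaccine-serotype pneumococcal disease in children who were initially randomized into the study", adds that the number of doses and withdrawal do not matter, and ends "The null hypothesis of no difference between the two groups in all randomized chldren will be tested".

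**The concern.** An intent-to-treat comparison keeps each child in the arm that chance assigned, whatever was then given. Section VI.B recognises that a wrong-code dose departs from the randomisation schedule, and then groups the child by that dose. Where the first dose came from the other arm, this is as-treated classification.

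The label matters because both primary outcomes are per-protocol: three doses on schedule, with onset or admission at least 14 days after the third. The intent-to-treat analysis of vaccine-serotype invasive disease is the protocol's check on those exclusions, so it should not itself regroup children by something that happened after randomisation. This is not a detail left open for a later analysis plan, because the protocol has fixed the rule.

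**Working it through.** **The plan's own figures.** No case count or power is stated for the intent-to-treat analysis. The stated targets belong to the per-protocol primary outcome (section IX.B). They reproduce with treated cases X ~ Binomial(n, p), p = 0.3/1.3 = 0.231 at 70% efficacy and equal follow-up, and lower limit of efficacy = 1 − pU/(1 − pU), where pU is the exact upper 97.5% limit for p.

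- n = 28: the lower limit exceeds 0 with 8 or fewer treated cases, probability 82.2%.
- n = 43: the lower limit exceeds 20% with 12 or fewer treated cases, probability 82.6%.

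Both meet the stated 80%. Wrong-code children are excluded from that analysis, so the choice of intent-to-treat grouping moves neither figure.

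**Which text governs the grouping.** Sections II.B and IX.C item 3 (and the same objective in the Protocol Summary) say who is included: randomised children with at least one dose. None says in which arm a wrongly dosed child is counted. Section VI.B item 5 is the only rule.

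**Which errors change the arm.**

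| Error | Arm under VI.B item 5 | Same as randomised? |
|---|---|---|
| First dose, code of the opposite arm | arm of the dose given | no |
| First dose, another code of the same arm | same arm | yes |
| Dose 2 or 3, any wrong code | arm of the correct first dose | yes |

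Only the first row is a defect.

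**Size.** The error rate e is not in the documents, so a range is shown. Assumptions: five codes per arm (the protocol gives ten codes and equal allocation, not the split), wrong codes chosen at random, and true efficacy 70%. A wrong code then belongs to the other arm with probability 5/9, so the share of children moved is c = 5e/9. Because later doses follow the first-dose code, a moved child is treated as having had the other product throughout.

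- Grouped by first dose received: efficacy = 70%.
- Grouped as randomised: RR = [0.3(1 − c) + c] / [(1 − c) + 0.3c], efficacy = 1 − RR.

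At e = 1%: c = 0.00556, RR = 0.30389/0.99611 = 0.3051, efficacy 69.49%.

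| e | Children moved, of 48,000 | Efficacy as randomised | Expected cases among moved children, per 28 / per 43 |
|---|---|---|---|
| 0.1% | 27 | 69.95% | 0.02 / 0.02 |
| 0.5% | 133 | 69.75% | 0.08 / 0.12 |
| 1% | 267 | 69.49% | 0.16 / 0.24 |
| 2% | 533 | 68.98% | 0.31 / 0.48 |
| 5% | 1,333 | 67.42% | 0.78 / 1.19 |

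The last column is 28c and 43c. These counts are borrowed from the primary analysis only to give a scale.

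**The case against.** The best defence is that the rule is prespecified, applies equally to both arms, and touches very few children in a secondary analysis. Staff are blinded to the ten codes, so a mix-up at the first visit has no evident route to depend on product or prognosis. All of that stands, and it limits the size of the problem. It does not make grouping by product received intent-to-treat.

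A reader might infer more than the documents support:

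- *That VI.B contradicts IX.C item 3.* It does not. IX.C item 3 defines the population and is silent on the grouping of wrongly dosed children.
- *That the whole analysis is as-treated and loses the protection of randomisation.* Every child outside the first row of the error table is grouped as randomised. Incomplete series and withdrawals, the main sources of selection in the per-protocol analysis, are expressly kept in.
- *That missing cards and movement between clinics drive the problem.* Section VI.B item 2 deals with these for children who already have a code, so they bear on doses 2 and 3, where the rule gives the randomised arm.
- *That one moved case would overturn the result.* At 28 cases a 20:8 split has a lower limit of about 5% and 19:9 has −9.9%. But that boundary belongs to the primary analysis, which excludes these children. No intent-to-treat case count is fixed, and at a 1% error rate fewer than 0.25 cases are expected among moved children on either scale.

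**Conclusion.** The rule is wrong as written, at low to moderate severity. For first-dose errors that cross arms, the analysis named intent-to-treat groups children as treated, and nothing elsewhere in the protocol corrects this. Under random errors it removes the dilution that an intent-to-treat analysis should show, and so slightly favours the vaccine: by about 0.05 to 0.5 percentage points of efficacy for error rates of 0.1% to 1%, and by 2.6 points at 5%. Those figures rest on the assumed five-and-five split of codes, random errors and 70% true efficacy. The real error rate is unknown, and the protocol expects it to be low. If errors were not random, the size and direction could not be predicted, but the documents give no evidence of that.

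**What to change.** Replace the last sentence of section VI.B item 5 with wording such as: *For intent-to-treat purposes each such child is counted in the arm of the vaccination code assigned at randomisation, whichever vaccine was given.* State the same grouping rule once in section IX.C item 3, so that population and grouping stand together. If the sponsor wants the first-dose grouping, report it as a sensitivity analysis labelled as-treated.

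The cost is one or two sentences, settled before unblinding. The assigned code is already on the randomisation list, in the clinic register and in the study database (sections VI.A item 4 and VI.B item 2). No sample size, case target or primary analysis changes.
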